Infection with human rhinovirus is a major cause of asthma exacerbations and is thought to be a significant contributor in COPD and other respiratory diseases. It is estimated that approximately 90% of rhinovirus serotypes use intercellular adhesion molecule-1 (ICAM-1) as their receptor. Induction of ICAM-1 expression promotes recruitment and activation of inflammatory cells. Treatments impacting on ICAM expression may offer a novel target to reduce the frequency and severity of upper and lower respiratory tract infection and hence reduce exacerbation rate in high risk patients. Nasal LPS challenge offers a model to upregulate ICAM expression and subsequently may have utility in early drug development studies determining “Proof of Mechanism”.

It has long been recognised that there is “one airway”, with a strong functional and immunological relationship between the nose and bronchi (6;7), especially in terms of infiltrating leukocytes and inflammatory mediators when comparing allergic rhinitis and allergic asthma (8). There is also the insight that patients with respiratory disease commonly have inflammation of both the airways and nasal passages, with a similar type of inflammatory infiltrate in lower and upper airways.

It is possible to obtain repeated samples of nasal exudates and mucosa cells before and after nasal challenge in a relatively non-invasive way by techniques such as nasal filter paper (9) (10), nasal lavage (11)., and nasal epithelial scrapes (Rhinoprobe curette) (12).

- Synthetic absorption matrix (SAM) strips can be placed on the turbinates to absorb nasal lining fluid (13). The nasosorption method has the advantage of directly sampling nasal secretions which are less diluted, and releasing fluid on spin filtration, with less protein binding than with filter paper. The SAM method of sampling can therefore pick up protein signals which are below the detection limits of nasal lavage.
- Nasal lavage is commonly performed to isolate leukocytes from the nasal mucosal surface by the nasal pool method of Greiff and colleagues (11).
- A plastic nasal curette (Rhinoprobe, Arlington Scientific) can be used to obtain epithelial cells for cytology (14) and mRNA gene expression studies (15;16). This method of sampling is almost painless, and has been extensively employed in adults and infants (17).

Nasal allergen challenge (NAC) is a model that has been increasingly used instead of inhaled allergen challenge to assess both topical and systemic new therapies for asthma and allergy (18). Using the NAC in phase II of drug development for asthma and allergic rhinitis it is possible to provide an early and reliable “Go/No Go” decision before embarking on large-scale, long-term and costly phase III studies.

Using our experience with NAC and novel sampling methodologies, we would like to develop a model of nasal challenge with LPS. Bacterial LPS is an active component of cigarette smoke (19), and nasal challenge with LPS has been studied in a variety of different models causing release of mediators such as TNF-α and MIP-1 (20-26). These mediators have been detected in nasal lavage, and we expect nasosorption to achieve much higher detectable levels of mediators.

**Previous administration of LPS to Man**

a. There is considerable published experience with administration of LPS to man.

Systemic injection of LPS intravenously causes a mild fever and decrease in FEV1 in healthy volunteers at 2ng/kg (27;28)(12383} and at 4ng/kg (29).

Inhaled LPS has been administered from a nebulizer at doses of 50g (30;31) and 60g (32).

Nasal LPS has been used in man with no reports of any local or systemic symptoms or adverse effects being caused (20-26). In subjects given a nasal spray, LPS at 25g per nostril has been given in two studies (24;25) and LPS at 50g per nostril was employed in a further study (26). The LPS source used in these studies is Sigma (catalogue no. L3129, E. coli serotype 0127:B8).

b. In mice and rats, acute LPS nasal challenge is routinely performed with 2.5mg/kg, and is given as 50g LPS as an acute intratracheal dose. The source of LPS used in these studies is Sigma (catalogue no. L3129, E. coli serotype 0127:B8).

c. We propose a highest dose of LPS of 100g per nostril (InvitroGen Ultrapure) since Sigma LPS is 1.5 to 3 times more potent. Hence, 100g of InvitroGen LPS has a potency similar to that of 50g of Sigma LPS, and this dose of Sigma material has been well tolerated in man (26).

# 2. Study Hypotheses and Objectives

The purpose of this study is to develop a safe and effective challenge model to LPS in terms of induction of ICAM-1, and so provide a robust framework for the clinical assessment of future anti-inflammatory therapies directed specifically against ICAM-1.

- 1. **Hypothesis**

The nasal ICAM-1, cellular and cytokine/chemokine responses will be reproducible and show a dose response in relation to the amount of LPS used to challenge.

**2.2 Primary Objective**

The principal research questions (primary end point, PEP):

- Can we develop a well tolerated, robust and reproducible (validated) nasal LPS challenge system in terms of ICAM-1 induction ?
- Can we document a dose response and time course to nasal LPS in terms of cell influx, cytokine and chemokine release, and nasal epithelial curettage (Rhinoprobe) mRNA expression ?
- To assess the unstimulated expression of ICAM-1 in nasal epithelial scrapes.
- To provide a nasal challenge method with LPS to enable a “proof of target pharmacology” for a therapy directed against ICAM-1 induction. This may also permit dosage optimisation in relation to clinical efficacy studies.

1. **Study Design**

5-way crossover study, randomized, single-blind, placebo-controlled, dose-response to LPS.

A single cohort of 15 healthy volunteers will be studied in a 5-way cross-over study (4 doses of LPS versus placebo), for a minimum of 12 to complete.

A balanced Latin square randomized design will be used.

Total study duration: 6-9 months

1. **Study population**

For this clinical study it is proposed to study healthy volunteers with no history of allergy, nor any other significant illnesses or therapy.

15 healthy volunteers will be recruited, for a minimum of 12 to complete

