## Regimen Assignment

Subjects will be assigned to a sequence in accordance with the randomisation schedule generated prior to the start of the study. The randomisation will be balanced over the 5 nasal challenge sequences and will be generated using RandAll, the GSK web-server based clinical trials randomisation validated system.

A description of each challenge sequence is provided in Table 1. The LPS dose corresponds to the dose administered to each nostril.

Table 1. Nasal LPS Dosage Regimen Sequence

| Sequence | Number of subjects receiving sequence | Nasal Challenge 1 | Nasal Challenge 2 | Nasal Challenge 3 | Nasal Challenge 4 | Nasal Challenge 5 |
| --- | --- | --- | --- | --- | --- | --- |
| 1 | 3 | placebo | 1μg LPS | 10μg LPS | 30μg LPS | 100μg LPS |
| 2 | 3 | 1μg LPS | 30μg LPS | placebo | 100μg LPS | 10μg LPS |
| 3 | 3 | 10μg LPS | 100μg LPS | 30μg LPS | 1μg LPS | placebo |
| 4 | 3 | 30μg LPS | 10μg LPS | 100μg LPS | placebo | 1μg LPS |
| 5 | 3 | 100μg LPS | Placebo | 1μg LPS | 10μg LPS | 30μg LPS |

A washout time of 12-28 days will be employed between challenges

1. **Samples and Measures**

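### The Latin square in Table 1 is balanced for period and allocation but not for preceding dose, so any LPS carry-over would distort the dose-minus-placebo contrasts unevenly

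*Protocol*

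**What the plan says.** The Study Design section, printed after section 2.2, states: "A balanced Latin square randomized design will be used". The section Regimen Assignment adds: "The randomisation will be balanced over the 5 nasal challenge sequences". Its Table 1 gives three subjects to each of five sequences:

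- Sequence 1: "placebo | 1μg LPS | 10μg LPS | 30μg LPS | 100μg LPS"
- Sequence 2: "1μg LPS | 30μg LPS | placebo | 100μg LPS | 10μg LPS"
- Sequence 3: "10μg LPS | 100μg LPS | 30μg LPS | 1μg LPS | placebo"
- Sequence 4: "30μg LPS | 10μg LPS | 100μg LPS | placebo | 1μg LPS"
- Sequence 5: "100μg LPS | Placebo | 1μg LPS | 10μg LPS | 30μg LPS"

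Below the table: "A washout time of 12-28 days will be employed between challenges". Section 8.1 describes the study as generating hypotheses, not testing them. Section 8.3.2 plans descriptive summaries by dose and time, and plots pre-dose ICAM-1 and TNF-α against period number.

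**The concern.** For a crossover, a statistician usually reads balanced to mean that each treatment follows each other treatment equally often, so that a first-order carry-over falls evenly on the treatments. Table 1 does not have this property. Section 2 makes a dose response part of the hypothesis, and section 2.2 lists documenting it among the principal questions. If a previous LPS challenge still affects the response at the next session, whether by priming, tolerance or residual inflammation, the comparator and the doses receive unequal shares of that effect. The shape of the dose-response curve is then distorted, and summaries by dose have nothing in them to remove the distortion.

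**Working it through.** **Inputs.** The five sequences and three subjects per sequence come from Table 1, so 5 × 3 = 15 subjects, as the protocol states. P is placebo; doses are µg per nostril. The size of any carry-over is an assumption, because the protocol gives none.

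**Step 1: what is balanced.** Every row and every column of Table 1 contains all five treatments once. Balance for period and for allocation is confirmed.

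**Step 2: count the ordered pairs.** Five sequences with four transitions each give 20 transitions.

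| Previous → next | P | 1 | 10 | 30 | 100 |
|---|---|---|---|---|---|
| P | – | 3 | 0 | 0 | 1 |
| 1 | 1 | – | 2 | 1 | 0 |
| 10 | 0 | 0 | – | 2 | 2 |
| 30 | 1 | 1 | 1 | – | 1 |
| 100 | 2 | 0 | 1 | 1 | – |

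Six pairs never occur: P→10, P→30, 1→100, 10→P, 10→1 and 100→1. The dose of 1 µg is preceded by P, P, P and 30. Placebo is preceded by 30, 1, 100 and 100.

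**Step 3: benchmark.** Enumerating the 5x5 Latin squares (56 with first row and first column fixed) shows that none contains more than 15 of the 20 ordered pairs. Table 1 contains 14, one fewer than the best. Its more unusual feature is the threefold P→1; the squares that reach 15 pairs repeat no pair more than twice.

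**Step 4: bias if carry-over exists.** Every subject is planned to receive every dose, and every dose occurs equally often in each period. With complete data, least squares with subject, period and treatment therefore gives the simple difference of means. The carry-over that a dose receives is the sum of the carry-overs from its predecessors, divided by five sequences. If only 100 µg carries over, by an amount c:

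- Placebo receives 2c/5 = 0.40c.
- 1 µg receives 0; 10 µg and 30 µg receive c/5 = 0.20c each; 100 µg receives 0.
- Dose minus placebo is biased by -0.40c, -0.20c, -0.20c and -0.40c for 1, 10, 30 and 100 µg.

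Other assumed shapes, with c the carry-over after 100 µg:

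| Carry-over shape | 1 − P | 10 − P | 30 − P | 100 − P |
|---|---|---|---|---|
| 100 µg only | -0.40c | -0.20c | -0.20c | -0.40c |
| Proportional to dose | -0.40c | -0.20c | -0.22c | -0.36c |
| Equal for every active dose | -0.60c | 0 | 0 | -0.20c |

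**Step 5: the same with 15 balanced sequences (listed under the fix).** Each treatment occurs three times per period, and each ordered pair occurs three times. Each dose then receives one fifth of the summed carry-over of all other treatments, so dose d minus placebo is biased by -0.20 × (carry-over of d). With 100 µg only, this is 0, 0, 0 and -0.20c. With equal carry-over from every active dose it is -0.20c throughout, the same for all doses.

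**Step 6: precision if carry-over is modelled.** Let σ² be the within-subject residual variance. Without carry-over terms both designs give 2σ²/15 = 0.133σ² for every contrast. With first-order carry-over terms:

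- Table 1: 0.240σ² for 1 − P, 0.141σ² for 10 − P, 0.163σ² for 30 − P, 0.195σ² for 100 − P, 0.240σ² for 10 − 1 and 0.244σ² for 30 − 1.
- Balanced set: (2σ²/15) × 19/18 = 0.141σ² for every contrast.

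For 1 − P the ratio is 0.240/0.141 = 1.70.

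**Step 7: incomplete data.** The protocol requires only 12 completers. Take simple means over 12 completers, with carry-over from 100 µg only. In Table 1, six subjects receive placebo after 100 µg and none receives 1 µg after it. Losing three subjects leaves three to six, so the 1 − P bias lies between -3c/12 = -0.25c and -6c/12 = -0.50c. In the balanced set, three subjects receive placebo after 100 µg and three others receive 1 µg after it. The bias then lies between -0.25c and +0.25c and averages zero over random losses.

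**The case against.** Much of the case on the other side stands.

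- *The word.* Regimen Assignment uses balanced for allocation over sequences, and Table 1 delivers that. Neither section claims balance for preceding dose, so a reader who infers that the protocol contradicts itself goes too far. The label is ambiguous, and the design is weaker than it could be.
- *The count.* Six missing pairs sounds severe, but five is the least that any single 5x5 square can reach.
- *Which contrast.* A reader might infer that 1 µg versus placebo is uniquely the worst affected. It is not: 100 µg versus placebo has the same -0.40c if only 100 µg carries over, and 30 versus 1 µg has a slightly larger adjusted variance (0.244σ²).
- *Scraping.* A reader might add repeated nasal scraping to the causes. Section 7.1 and the Study Schedule apply the same scraping in every session, placebo included. Its residue depends on how many sessions came before, not on which dose. That is a period effect, and Table 1 balances it.
- *Whether carry-over exists.* The protocol sets a washout of 12-28 days and contains no evidence of an effect lasting that long. Section 8.3.2 examines pre-dose values by period and the return to baseline after 24 h. This helps, but a plot by period number mixes subjects with different preceding doses and does not show a dose-dependent residue directly.
- *The variance penalty.* The protocol states no carry-over-adjusted model, so the larger variance matters only if one is fitted.

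**Conclusion.** The point holds as a minor design weakness. That Table 1 lacks balance for preceding dose is exact and needs no assumption. The consequence is conditional: it requires a dose-dependent LPS carry-over that survives the washout. Under that condition the dose-minus-placebo contrasts are distorted unevenly, by 0.20c to 0.40c if only 100 µg carries over, with 1 µg versus placebo among the most exposed. If carry-over raises the response, the differences from placebo are understated. The documents do not support a conclusion that the results will be biased, because c is not known and may be zero. The exploratory, descriptive purpose keeps the severity low; the point is worth acting on because the remedy costs so little.

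**What to change.** Before the schedule is generated, replace Table 1 with these 15 sequences, one per subject (P = placebo; figures in µg per nostril):

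- Square A: P-1-10-30-100; 1-10-100-P-30; 10-100-30-1-P; 30-P-1-100-10; 100-30-P-10-1
- Square B: P-10-1-30-100; 1-100-10-P-30; 10-30-100-1-P; 30-1-P-100-10; 100-P-30-10-1
- Square C: P-10-100-1-30; 1-100-30-10-P; 10-30-P-100-1; 30-1-10-P-100; 100-P-1-30-10

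A standard 10-sequence Williams design is also balanced for preceding dose, but 15 subjects cannot be divided equally over 10 sequences.

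State in the Study Design section what balanced means: period, allocation and preceding dose. Change the reference to five sequences in Regimen Assignment to 15. In section 8.3.2, plot pre-dose values by preceding dose as well as by period number.

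The cost is a new randomisation list and 15 sequences to administer instead of five. Subjects, dose levels, number of periods, washout and the three subjects starting on each treatment stay as they are. The rule in section 8.2.1 that a replacement takes the sequence of the subject replaced still works and helps to restore balance after a loss. The new set does not remove all bias: each dose keeps -0.20 of its own carry-over against placebo, and losses disturb the exact balance. If Table 1 is kept, the protocol should say that it is balanced for period and allocation only.

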**4.1 Inclusion criteria**

- Males and females aged 18 to 60 years
- Current non-smokers for last 6 months (<5 cigs per week), with a smoking history of <5 pack years
- BMI 20-30 kg/m2

**4.2 Exclusion criteria**

- History of allergy
- Upper airway infection in 2 weeks before screening
- Lower respiratory tract infection in past 3 months
- Treatment with local or systemic corticosteroids during previous 2 months
- Signs or symptoms of chronic rhinitis, hypertrophy of turbinates, major septum deviation, nasal polyposis or recurrent sinusitis
- Previous nasal or sinus surgery
- Clinically significant cardiovascular, hepatic, GIT, renal, endocrine, infective, haematological, neurological, dermatological, neoplastic conditions, gastro-oesophageal reflux, depression, TB
- Participation in a therapeutic drug trial in the prior 30 days.
- Medical therapy other than that permitted for contraception.
- Positive pregnancy test
- Inability or unwillingness to use contraception if the patient is a female of child-bearing age.
- History of drug abuse or urine test showing evidence of recreational drug abuse

**5. Lipopolysaccharide (LPS) for Nasal Challenge**

**5.1 LPS from Invivogen**

The highest purity commercially available LPS will be utilised.

We shall employ ultrapure LPS from *Escherichia coli* 0111:B4 (Invivogen Ltd, San Diego, Ca)

This material is authorized for research and laboratory use only, and not for drug use in the USA.

**5.2 Regulatory Aspects**

LPS is given as a challenge agent, to elicit an inflammatory response, and not employed for therapeutic benefit.

Hence the LPS is regarded by the UK regulatory authority (the Medicines and Healthcare Regulatory Authority, MHRA) as a Non-Investigative Medicinal Product (non-IMP) (33).

For this reason, LPS does not have to be manufactured according to Good Manufacturing Practice (GMP).

The relevant contact person at the MHRA, Clinical Trials Dept is [name].

**5.3 LPS Stock and Dilution on Day of Use**

5mg of LPS will be diluted in 0.5ml saline to make a single stock of LPS, 0.5ml at 10mg/ml. This dilution will be performed by a physician in the presence of a senior nursing or technical staff, and appropriate documentation will be signed when making up stock as well as when aliquoting and diluting on the day of challenge.

This 10mg/ml stock will be aliquoted as follows:

10 aliquots of 25l = 250l total volume

25 aliquots of 10l= 250l total volume

There will be storage of all aliquots at -80C, for a maximum of 1 year, with thawing less than 3h before use.

| **Dilution of stock (10mg/ml)**  **on morning of administration** | **LPS for nasal delivery** | **LPS nasal dose g per nostril as 100l actuation** |
| --- | --- | --- |
| 25l stock  + 225l saline | 1000g/ml, vol 250l | 100 |
| 10l stock  + 290l saline | 300g/ml, vol 300l | 30 |
| 10l stock  + 990l saline | 100g/ml, vol 1ml | 10 |
| 10l stock  + 990l saline  ***Then dilute 10 times***  ***(100l of diluted stock + 900l of saline)*** | 10g/ml, vol 1ml | 1 |

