**5.4 LPS administration**

A physician shall prepare the LPS solution, load the Pfeiffer Bidose device and complete a record form. The procedure will be checked and signed by a senior member of ICRRU staff.

LPS solutions (Ultrapure LPS E-Coli 0111:B4 (*Invivogen*) and placebo will be administered from a Pfeiffer Bidose nasal delivery device by a physician.

This is a high quality non-GMP source of LPS.

LPS solution (250l) will be prepared at 10, 100, 300 and 1000g/ml,

100l is administered to each nostril, both nostrils will be sprayed

The dose per nostril corresponds to 1, 10, 30 and 100g

Weights will be recorded before and after each actuation from the Pfeiffer Bidose.

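### Section 5.3 supplies 10 aliquots for the 100 µg challenge where Table 1 needs 15 (12 for the minimum of completers), and the 500 µl stock is too small for 15 subjects under the written dilutions

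*Protocol*

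**What the plan says.** Protocol section 5.3 dissolves 5 mg of LPS "to make a single stock of LPS, 0.5ml at 10mg/ml". It then divides the whole stock into two aliquot sizes: "10 aliquots of 25l = 250l total volume" and "25 aliquots of 10l= 250l total volume". The micro sign is missing from these volumes; they are read here as microlitres, the only reading that fits a 0.5 ml stock.

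The dilution table in 5.3 assigns the 25 µl size to the 100 µg dose alone ("1000g/ml, vol 250l"). The 10 µl size serves the other three: the 30 µg dose ("300g/ml, vol 300l"), the 10 µg dose ("100g/ml, vol 1ml"), and the 1 µg dose, which is a further tenfold dilution, also made up to 1 ml. Dilution is done on the morning of use, with thawing less than 3 hours beforehand.

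Section 5.4 gives 100 µl per nostril and says that "both nostrils will be sprayed". Table 1 gives every LPS dose once to each of 15 subjects, three per sequence. The study population section states that "15 healthy volunteers will be recruited, for a minimum of 12 to complete". Section 8.2.1 allows replacement subjects. No second stock is mentioned, and nothing says whether one preparation may serve several subjects.

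**The concern.** The aliquot counts in 5.3 are fixed numbers that should follow from the number of subjects and the volume each challenge uses. For the top dose they do not.

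The study aims to show a dose response to LPS and the reproducibility of the challenge, and each subject serves as his or her own control. If the top-dose aliquots run out, some subjects miss the 100 µg challenge or receive it from a stock that the protocol did not plan. A second stock made part-way would add any stock-to-stock difference in concentration to the comparison, and it could split one subject's doses across two stocks.

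**Working it through.** **Inputs**
- Stock: 5 mg in 0.5 ml (5.3).
- Aliquots: 10 of 25 µl and 25 of 10 µl (5.3).
- Volume per challenge: 2 × 100 µl = 200 µl (5.4).
- Subjects: 15, each receiving every dose once, three per dose in each period (Table 1); at least 12 to complete.

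**The plan's own figure.** 5 mg / 0.5 ml = 10 mg/ml. 10 × 25 + 25 × 10 = 250 + 250 = 500 µl. This reproduces, and nothing is left over.

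**Challenges per preparation** = prepared volume / 200 µl, rounded down.

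| Dose per nostril | Stock used | Prepared volume | Challenges served |
|---|---|---|---|
| 100 µg | 25 µl | 25 + 225 = 250 µl | 1 |
| 30 µg | 10 µl | 10 + 290 = 300 µl | 1 |
| 10 µg | 10 µl | 10 + 990 = 1000 µl | up to 5 |
| 1 µg | 10 µl, then 100 + 900 | 1000 µl | up to 5 |

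Section 5.4 speaks of preparing 250 µl at each concentration. If 250 µl is set aside per challenge, the last column becomes 1, 1, 4 and 4, and no result below changes.

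**100 µg dose.** One aliquot serves one subject, and the 50 µl left over cannot dose another. Ten aliquots give 10 administrations. Shortfall: 15 − 10 = 5 for all subjects, 12 − 10 = 2 for the minimum.

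**Pooling.** Five subjects dosed on one day need 5 × 200 = 1000 µl, which is 4 aliquots, so pooling saves one. With one to four subjects on a day it saves none, and Table 1 gives 100 µg to three per period. Pooling all ten preparations without loss would give 2500 / 200 = 12.5 doses, still short of 15.

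**All doses.** The 30 µg dose needs one 10 µl aliquot per subject. The 10 and 1 µg doses need one each per subject, or one per three subjects if three share on the same day.

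| | 12 subjects | 15 subjects |
|---|---|---|
| 25 µl aliquots (10 provided) | 12 | 15 |
| 10 µl aliquots, no sharing (25 provided) | 36 | 45 |
| 10 µl aliquots, three sharing | 12 + 4 + 4 = 20 | 15 + 5 + 5 = 25 |
| Stock, no sharing (500 µl provided) | 300 + 360 = 660 µl | 375 + 450 = 825 µl |
| Stock, three sharing | 300 + 200 = 500 µl | 375 + 250 = 625 µl |

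If the 1 µg dose is also drawn from the same day's 10 µg dilution, the small aliquots fall to 12 + 4 = 16 and 15 + 5 = 20, and the stock to 300 + 160 = 460 µl and 375 + 200 = 575 µl. For 15 subjects that still exceeds 500 µl.

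**Lower bound for 15 subjects.** The two doses that cannot share need 15 × 25 + 15 × 10 = 375 + 150 = 525 µl, before any 10 or 1 µg dose.

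**A discrepancy in the 30 µg row.** 10 µl of stock in 300 µl gives 10,000 × 10 / 300 = 333 µg/ml, not the stated 300. These figures need reconciling separately. The bound does not depend on it: 300 µl at 300 µg/ml contains 90 µg, or 9 µl of stock, and 375 + 15 × 9 = 510 µl is still above 500 µl.

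**When the top dose would run out.** Table 1 places 100 µg in period 1 for sequence 5, period 2 for sequence 3, period 3 for sequence 4, period 4 for sequence 2 and period 5 for sequence 1. If all subjects progress in parallel (an assumption), nine aliquots are used by the end of period 3 and the tenth in period 4. Two subjects in sequence 2 and all three in sequence 1 are then without a top-dose aliquot.

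**The case against.** The strongest reply is that this is a supply detail with slack. The amount of LPS is sufficient: 15 × 2 × (100 + 30 + 10 + 1) = 4230 µg, or 4.23 mg of the 5 mg. Low-dose preparations of 1 ml can be shared. Another stock can be made by the same witnessed procedure. The analysis is descriptive and hypothesis-generating, and Table 1 places every dose in every period, so a change of stock by calendar time need not line up with dose.

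Much of this stands, and it rules out three stronger readings.

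- A reader might infer that even 12 subjects cannot be dosed from this stock. The documents do not support that. With three subjects sharing each low-dose preparation, 12 subjects need exactly 500 µl, so a different split could serve them, though without loss or spares.
- A reader might set 25 small aliquots against 45 and call it a firm shortage. Sharing is neither stated nor excluded, and with three sharing, 25 suffice for 15 subjects. The figures 45, 825 µl and 660 µl are upper bounds.
- A reader might infer that the dose response will be confounded by batch. The documents give no stock-to-stock variability, so the size of any such effect is unknown. Nor is a model specified to which a batch term could be added.

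What does not stand is that the slack repairs the written plan. Sharing does not help at 100 µg or 30 µg. The mass is enough only if the volumes differ from those in the table. The text describes a single stock and gives no rule for another. Balance over periods does not prevent a subject's top dose from coming from a different stock than the lower doses.

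**Conclusion.** Wrong as written. The written aliquots cover 10 administrations of 100 µg, against 15 scheduled and 12 needed for the minimum of completers. This rests only on the volumes in 5.3 and 5.4 and on aliquots being used as the dilution table shows.

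For 15 subjects the whole stock is also too small under the written dilutions: at least 525 µl, 625 µl with three-way sharing of the two lowest doses, and at most 825 µl without sharing, against 500 µl. For 12 subjects the failure lies in the split. The volume could just suffice if the 10 and 1 µg subjects attend in threes on the same day, nothing is lost, and no aliquot goes to a subject who later drops out.

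The consequence is one of supply and stock consistency in a within-subject comparison, not an error in the statistical analysis. It can be corrected cheaply before the first challenge.

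**What to change.** Before dosing starts, reconcile the stock volume and aliquot counts in section 5.3 with Table 1 and the 15 planned subjects.

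- Prepare one homogeneous stock at the start, large enough for at least 15 aliquots of 25 µl, the 10 µl aliquots, and spares for replacement subjects. Before spares this means 625 µl (6.25 mg at 10 mg/ml) with three-way sharing, up to 825 µl (8.25 mg) without. The 1-year storage limit in 5.3 covers the stated study duration of 6 to 9 months.
- State whether 10 and 1 µg preparations may be shared between subjects on the same day, and set the number of 10 µl aliquots to match: 25 with three sharing, 45 without, plus spares.
- If a second stock is still needed, switch between subjects rather than within a subject, and record the stock batch for each challenge in the listings and plots.

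The cost is some additional LPS and corrected counts in 5.3. No dose, schedule or analysis changes.

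### As written, the section 5.3 recipe for the 30 µg LPS dose makes 333 µg/ml (33.3 µg per nostril), 11.1% above the stated 300 µg/ml and 30 µg

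*Protocol*

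**What the plan says.** Protocol section 5.3 defines the stock: "5mg of LPS will be diluted in 0.5ml saline to make a single stock of LPS, 0.5ml at 10mg/ml". The stock is divided into aliquots of 25 µl and 10 µl, the latter described as "25 aliquots of 10l= 250l total volume". (The µ sign is missing from the extracted text throughout sections 5.3 and 5.4. Table 1 prints µg.)

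The second row of the dilution table takes one 10 µl aliquot and reads "290l saline | 300g/ml, vol 300l", with 30 in the dose column. It therefore states a concentration of 300 µg/ml, a final volume of 300 µl and a dose of 30 µg per 100 µl actuation.

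Section 5.4 repeats the target concentrations (10, 100, 300 and 1000 µg/ml), gives 250 µl as the volume of solution prepared, and adds "100l is administered to each nostril, both nostrils will be sprayed" and "The dose per nostril corresponds to 1, 10, 30 and 100g". Table 1, under Regimen Assignment, uses the label 30 µg once in each of the five sequences. None of these places calls 30 µg nominal, rounded or approximate.

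**The concern.** The row gives a stock volume, a saline volume, a final volume and a final concentration. Together with the stock strength these leave nothing free, and they do not agree. Someone who follows the recipe departs from section 5.4 and Table 1. Someone who works to the concentration in section 5.4 departs from the recipe.

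Two things are at stake. The dose given to volunteers should be the dose that the protocol states. And sections 2.2 and 8.1 make the dose response to LPS part of the primary objective, so each dose should be reported under its true value. The discrepancy is systematic: it would be the same for every subject dosed from the recipe, so averaging over subjects would not remove it.

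**Working it through.** **Inputs** (Protocol sections 5.3 and 5.4)

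- Stock: 5 mg / 0.5 ml = 10 mg/ml = 10,000 µg/ml. This reproduces the stated stock strength.
- Delivered volume: 100 µl = 0.1 ml per nostril.

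**Formulas**

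- Concentration = stock concentration × stock volume / (stock volume + saline volume)
- Dose per nostril = concentration × 0.1 ml

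**Each row of the dilution table**

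| Stated dose | Recipe | Calculation | Result | Stated | Agrees |
| --- | --- | --- | --- | --- | --- |
| 100 µg | 25 µl + 225 µl | 10,000 × 25/250 | 1000 µg/ml, 100 µg | 1000 µg/ml, 100 µg | yes |
| 30 µg | 10 µl + 290 µl | 10,000 × 10/300 | 333.3 µg/ml, 33.3 µg | 300 µg/ml, 30 µg | no |
| 10 µg | 10 µl + 990 µl | 10,000 × 10/1000 | 100 µg/ml, 10 µg | 100 µg/ml, 10 µg | yes |
| 1 µg | as for 10 µg, then diluted 10 times | 100/10 | 10 µg/ml, 1 µg | 10 µg/ml, 1 µg | yes |

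**Size of the discrepancy**

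- Relative: 333.3/300 − 1 = 11.1%.
- Over both nostrils: 2 × 33.3 = 66.7 µg against 2 × 30 = 60 µg.
- Same result by mass: 300 µl at 300 µg/ml would hold 0.3 × 300 = 90 µg, but the recipe puts in 0.010 ml × 10,000 µg/ml = 100 µg.

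**Could another reading rescue the row?**

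- 290 µl as the total volume: 10,000 × 10/290 = 344.8 µg/ml.
- 300 µl of saline added to 10 µl: 10,000 × 10/310 = 322.6 µg/ml.
- Neither gives 300. The printed final volume of 300 µl confirms 10 + 290, so the lost µ signs do not explain the mismatch.

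**Who would be affected**

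In Table 1 the 30 µg dose falls in challenge 4, 2, 3, 1 and 5 for sequences 1 to 5, once each, with 3 subjects per sequence: 5 × 3 = 15 planned subjects. The protocol needs at least 12 to complete, and a subject who withdraws before that session does not receive the dose.

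**Would the planned checks find it?**

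Section 5.4 weighs the device before and after each actuation, which checks the volume delivered and not the concentration. The second-person check and signature can confirm that the recipe was followed, but the recipe is what disagrees with the label.

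**A related mismatch**

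Section 5.4 gives 250 µl as the prepared volume. In section 5.3 only the 100 µg row makes 250 µl. The 30 µg row makes 300 µl, and the other two make 1 ml.

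**The case against.** The case against giving this much weight runs as follows, and most of it stands.

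- **No numeric dose axis is planned.** A reader might infer that a dose-response curve will be fitted with one point misplaced, by log10(33.3/30) = 0.046. Section 8.3.2 does not support this. It plans descriptive summaries by dose and time, time plots with doses as separate lines, and box plots by dose and time. Dose acts as an ordered category, and the order 1, 10, 33.3, 100 is unchanged. Section 8.1 calls the study hypothesis generating.
- **The dose spacing is no worse.** The steps around this dose would be 33.3/10 = 3.33 and 100/33.3 = 3.00, where the stated doses give 30/10 = 3.00 and 100/30 = 3.33. They only change places.
- **No exposure limit stated in the protocol is crossed.** A reader might infer a safety problem. The document does not show one: 33.3 µg is a third of the highest planned dose, 100 µg, which every sequence also contains and whose row is correct.
- **It is not certain that every subject would be misdosed.** A reader might take all 15 as affected. That holds only if the recipe is followed, and section 5.4 separately calls for 300 µg/ml. It also holds only for subjects who reach that session.

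None of this touches the arithmetic. The row contradicts itself without any outside figure, and nothing in the protocol says whether the recipe or the label governs.

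**Conclusion.** The point holds as an internal contradiction in a preparation instruction. As written, the recipe makes 333.3 µg/ml and 33.3 µg per nostril, 11.1% above the stated 300 µg/ml and 30 µg. The stock strength and the other three rows are right.

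The consequence rests on two assumptions: that staff follow the recipe rather than the stated concentration, and that the subject reaches the session in question. Under these, the dose is mislabelled in one session per subject, for up to 15 planned subjects, and the planned weighing would not reveal it.

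The effect on the results is modest. What is wrong is that the dose given would differ from the dose stated and reported, in a study whose aim is to characterise a dose response. It should be corrected because it is an unambiguous error in a dosing instruction and costs almost nothing to remove, not because it threatens a planned conclusion.

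**What to change.** Before any dose is mixed, reconcile the four elements of the second dilution row (recipe, concentration, final volume and stated dose) with one another, with section 5.4 and with Table 1. Settle the 250 µl volume in section 5.4 at the same time, since it matches only one row of section 5.3. Which figure is kept is for the sponsor to decide.

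In all summaries and plots by dose, label this dose with the amount that the final recipe makes.

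The cost depends on the choice. If the recipe is changed to match the label, only the one table row changes, and the concentrations and doses in section 5.4 and Table 1 can stay as they are. If the label is changed to match the recipe, the stated concentration and dose in that row, in section 5.4 and in Table 1 change too. Correcting the volume in section 5.4 is a short text edit in either case. Neither route alters the design, the sample size or the planned analyses.
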